## 3.4. Treatments

### 3.4.1. Investigational therapy and reference therapy

We want to test prolonged release pasireotide 60 mg.

No treatment for the prevention of postoperative axillary lymphoceles has been granted a marketing authorization to date.

The control group will receive an intramuscular placebo injection (physiological serum).

### 3.4.2. Treatment assignment

Patients will be randomized to receive either an injection of prolonged release pasireotide 60 mg or a placebo injection (physiological serum), which will be administered intramuscularly 7 to 10 days before scheduled surgery.

Randomization will be stratified on

1. whether or not a neo-adjuvant treatment has been administered prior to surgery.
2. overweight/obesity with a BMI > 25
3. the including center

### 3.4.3. Blind procedure

The procedure will be conducted double blind: neither the patients nor the surgeon in charge of the patients will be informed of the type of treatment administered.

Only the consultation nurse will be informed of the treatment administered because pasireotide is suspended prior to injection. On the other hand, this nurse will not be present during the patient's hospital stay or subsequent visits warranting aspiration. In fact, these consultations are not held in the same location in either of the two including centers.

Randomization will be carried out by the Statistics Team at Hôpital Saint Louis in charge of the project (only one randomization list for both centers). The doctor who has included the patient will contact the randomization center which will put in touch (telecopy) with the nurse who will practice the injection. Thus, this last one will reconstitute the pasireotide or prepare the placebo.

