6.1. Statistical methods to be used [28](#__RefHeading___Toc246224633)

6.2. Efficacy evaluation: [28](#__RefHeading___Toc246224634)

6.3. Safety assessment [28](#__RefHeading___Toc246224635)

6.4. Number of subjects [28](#__RefHeading___Toc246224636)

6.5. Primary endpoint analysis [28](#__RefHeading___Toc246224637)

6. 6. Rules for discontinuation [29](#__RefHeading___Toc246224638)

Summary of Protocol

1. **Background**

The principal morbidity following axillary node dissection within the scope of breast cancer surgery is the post-operative development of lymphocele. According to the literature, incidence can vary from 4 to 89% depending on the type of surgery, whether or not a drain is inserted or a compression dressing applied and the time at which the drain is removed… In our experience, the incidence is 40% [IGR (Gustave Roussy Institute) data focusing on 70 patients between November 2008 and February 2009].

Encouraging results in terms of reducing postoperative lymphoceles as well as drainage duration and volume using Octreotide have been recorded in two recent studies. A new molecule developed by Novartis Laboratories, namely pasireotide, is a somatostatin analog possessing strong affinity for several somatostatin receptors (30 to 40 times greater for sst1 and sst5, 5 times greater for sst3 and equivalent for sst2)

1. **Purpose**

The purpose of this trial is to assess the efficacy of a pre-surgical injection of pasireotide LAR in reducing the postoperative incidence of symptomatic lymphoceles following axillary node dissection.

The secondary objectives are to assess the efficacy of prolonged release pasireotide on the duration of postoperative drainage, the daily drainage volume, the total drainage volume, the number of repeated lymphocele aspirations and the volume, the total volume of lymph aspirated, the incidence of postoperative febrile episodes, the length of hospital stay, and the length of time to onset of adjuvant chemotherapy. It is also to assess the safety of prolonged release pasireotide.

1. **Trial design**

We recommend a prospective, randomized, two-center trial according to a Bayesian design with a control arm receiving a placebo.

1. **Trial population**

All female patients for whom mastectomy - axillary node dissection is indicated at the pre-surgical stage will be eligible for inclusion. Control population of an identical size: randomization 1:1.

1. **Study Procedure**

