# 6. Statistical methods

## 6.1. Statistical methods to be used

We recommend a prospective, randomized, two-center trial according to a Bayesian design with a control arm receiving a placebo.

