## 6.5. Primary endpoint analysis

The statistical analysis will be carried out sequentially after observing the principal criterion (i.e. success is defined as a total volume of lymphoceles following single or repeated aspiration ≤ 60 cc in the 28 days following surgery or a routine aspiration volume on the 28th day ≤ 120cc) of each patient included for each randomization group, with or without treatment.

It involves estimating the probability of a response in each group (proportion of patients who will not have undergone lymphocele aspiration or the aspiration of a total volume of ≤ 60cc or ≤ 120cc for the aspiration carried out on the 28th day after surgery) using a Bayesian design based on a beta-binomial model (16,17). With the Bayesian approach, the response rate in each group (*i*) is considered as a random variable *primarily* of density focused on the anticipated response rate of 80% in the group receiving treatment and 60% in the treatment-free group, which will be sequentially updated as the observations are made according to a so-called *a posteriori* law.

*A priori* density will be selected for each group from the Beta conjugated laws group, defined by its two parameters *ai*and *bi* (with a life expectancy = and variance = , with *i=1,2* according to the group considered). The Bayesian estimator of the response rate in each group will be expectancy of the *a posteriori* law, i.e. the Beta law of parameters *Ani* and *Bni* , defined on the basis of those of the *a priori* law and the number *ni* of inclusions, as shown below. *Ani=a+ri* and *Bni=b+ni-ri,* where *ri* represents the number of responses observed on the *ni* included in the *i* group. The following estimator is, therefore, obtained: .

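### Randomisation is stratified on three factors that the stated primary analysis never uses, and the remark about a single list needs reconciling with stratification by centre

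*Protocol*

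**What the plan says.** Section 3.4.2 names three stratification factors: "whether or not a neo-adjuvant treatment has been administered prior to surgery", "overweight/obesity with a BMI > 25" and "the including center". Section 6.1 makes this a two-centre trial, and the Summary of Protocol sets the allocation ratio: "Control population of an identical size: randomization 1:1".

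Section 3.4.3, on blinding, gives the randomisation to one statistics team and adds in parentheses "only one randomization list for both centers". It continues: "The doctor who has included the patient will contact the randomization center". Neither section mentions sub-lists, blocks or minimisation.

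Section 6.5 estimates the response rate in each group "using a Bayesian design based on a beta-binomial model". The posterior parameters are the prior parameters updated by the number of responses and the number of inclusions in that group, and by nothing else. The four criteria in section 6.6 also use no stratification factor.

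**The concern.** There are two separate issues.

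**Analysis.** Factors are normally chosen for stratification because they are thought to affect the outcome. Stratifying makes the arms more alike on them, so the treatment difference varies less from trial to trial. An analysis that pools each arm into one binomial count does not recognise this, and its interval for the difference is wider than it needs to be. The trial has 90 patients and section 6.4 states no power or precision target, so precision that costs nothing is worth keeping. Section 6.5 does not leave the model open; it fixes an estimator without the factors.

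**Allocation.** Someone building the schedule from section 3.4.2 would prepare a sequence for each combination of factors. Someone building it from section 3.4.3 alone could prepare one unstratified sequence. The allocation method has to be settled before the first patient and cannot be repaired in the analysis plan.

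**Working it through.** **Inputs from the protocol.** 90 patients, 45 per arm (6.4); anticipated success 60% on control and 80% on treatment (6.5); two centres (6.1); three stratification factors (3.4.2). The protocol states no precision figure that could be reproduced first.

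**Assumptions, not in the protocol.** Each factor is present in 50% of patients; permuted blocks of 4; the same odds ratio for success for each factor, set at 1, 1.65, 2.72 or 4.48. Each scenario has 8,000 simulated trials.

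**Step 1, strata.** 2 × 2 × 2 = 8 strata; 90/8 = 11.25 patients per stratum, about 5.6 per arm.

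**Step 2, unadjusted standard error by formula.** √(0.60 × 0.40/45 + 0.80 × 0.20/45) = √(0.40/45) = 0.0943. The simulated mean model standard error is 0.0932. The small shortfall arises because observed rates are plugged in.

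**Step 3, unadjusted analysis after stratified randomisation.**

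| Assumed odds ratio per factor | Mean difference (true 0.20) | Actual SD | Mean model SE | SD/SE | Coverage of 95% interval |
|---|---|---|---|---|---|
| 1 | 0.2014 | 0.0947 | 0.0932 | 1.016 | 94.4% |
| 1.65 | 0.1987 | 0.0930 | 0.0932 | 0.998 | 94.8% |
| 2.72 | 0.1990 | 0.0893 | 0.0932 | 0.958 | 95.7% |
| 4.48 | 0.2003 | 0.0848 | 0.0933 | 0.909 | 96.7% |

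The mean difference stays within 0.002 of the truth, so there is no bias. An interval matched to the actual SD would be narrower by about 0%, 4% (1 − 0.958) and 9% (1 − 0.909) for odds ratios of 1.65, 2.72 and 4.48. Put the other way, the nominal interval is about 0%, 4% and 10% wider than needed (0.0933/0.0848 = 1.10). In points, the full width 2 × 1.96 × 0.0932 is 36.5. Matched to the actual SD it would be 2 × 1.96 × 0.0893 = 35.0 or 2 × 1.96 × 0.0848 = 33.2. Simulation error is about 1/√(2 × 8,000) = 0.8% on each SD and √(0.95 × 0.05/8,000) = 0.24 points on coverage.

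**Step 4, rough cross-check.** If each factor moves success from 50% to 70%, it explains 0.5 × 0.5 × 0.20² / (0.60 × 0.40) = 0.01/0.24 = 4.2% of the control-arm variance, and three factors explain 12.5%. √(1 − 0.125) = 0.935, or 6.5% narrower. This assumes perfect balance and control-arm variance in both arms, so it lies on the high side. The 50% to 70% shift is an odds ratio of (0.7/0.3)/(0.5/0.5) = 2.33, for which Step 3 suggests between 0% and 4%.

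**Step 5, only if the list were really unstratified.** For a factor present in 50% of patients, the between-arm gap in prevalence has SD √(2 × 0.25/45) = 0.105, and a gap of at least 10 points has probability 0.34. If the factor shifts success by 20 points, a gap of 10 to 20 points moves that trial's observed difference by 0.20 × 10 = 2 to 0.20 × 20 = 4 points. The simulated mean imbalance between arms within one centre is about 3.8 patients (95th percentile 9), against about 1.4 (95th percentile 3 to 4) with stratified blocks. The mean difference is still 0.20 to within 0.002, and coverage is 94.0% to 94.9%: the unadjusted interval already allows for this chance imbalance.

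**The case against.** **A reader might infer that sections 3.4.2 and 3.4.3 contradict each other.** The text does not go that far. The remark on a single list is a parenthesis in the blinding section, in a sentence about who performs the randomisation, and the next sentence has the including doctor contact a central service. One centrally held schedule, as opposed to a list at each site, is a natural reading, and such a schedule can contain the strata. What stands is that the protocol does not say so and that the literal wording fits poorly with centre as a stratification factor.

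**A reader might infer that leaving out the factors biases the result.** It does not. The unadjusted comparison is unbiased under either kind of list, and its interval is about right or mildly conservative.

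**The interval for a difference is not one the protocol defines.** Sections 6.5 and 6.6 work with a separate posterior for each group. For a single arm's rate, standardising to all 90 patients gains only about half as much: with 12.5% explained variance, √(1 − 0.125/2) = 0.968, or about 3% narrower. This objection stands. The gain computed above applies to a between-arm comparison, which would have to be added.

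**Adjusted analyses are often placed in the statistical analysis plan, and this is a 90-patient phase II trial.** Both points are fair, and the plan is not at hand. The point still holds against the protocol, because section 6.5 fixes an estimator that excludes the factors.

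**Replacing the model outright would disturb the stopping rules.** This is correct. The criteria in section 6.6 are built on the beta-binomial posterior and its predictive distribution, so a regression should not replace that model during monitoring.

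**Conclusion.** The point holds as a free improvement. It is not an error in the analysis. The trial stratifies on three factors, and the stated primary analysis uses none of them. If the factors are prognostic, the cost is some precision in the treatment difference: from nothing at an assumed odds ratio of 1.65 per factor to an interval about 9% narrower at 4.48. These figures rest on assumed prevalences, odds ratios and block size, and no figure stated in the protocol changes.

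The single-list remark is an ambiguity to be reconciled. The imbalance figures in Step 5 of the working apply only if the list is truly unstratified, which section 3.4.2 gives no reason to expect. They describe chance imbalance in a single trial and not systematic bias.

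**What to change.** 1. **Analysis (sections 6.5 and 6.6).** Keep the beta-binomial model for sequential monitoring and leave the section 6.6 criteria as they are. Add to the final efficacy analysis a between-arm comparison adjusted for neo-adjuvant treatment, BMI above 25 and centre. One option is a Bayesian logistic regression with weak priors, reporting the standardised difference in success proportions and the posterior probability that it exceeds zero. Show the unadjusted result beside it.
2. **Allocation (sections 3.4.2 and 3.4.3).** Replace the parenthesis with a sentence stating either that the statistics team holds one central schedule with a blocked sub-list for each of the eight strata, or that allocation is by central minimisation on the three factors.

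The cost is a second model at the final analysis and a few sentences of protocol text. No extra patients or data are needed: centre and the other two factors must be known at randomisation, and BMI and neo-adjuvant treatment are recorded at V1 in the section 3.5 schedule.

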### 3.4.4. Concomitant treatments

Other treatments received by the patient during her hospital stay will be listed and attached to the CRF.

### 3.4.5. Treatment compliance

Since treatment comprises a single injection adminstered at the hospital by a state registered nurse, there are no treatment compliance issues.

### 3.4.6. Treatment packaging and management

Pasireotide will be provided by Novartis® Laboratory. The medicinal product will be repackaged and re-labelled for this study by an external service provider (LC2) and then redistributed to each center depending on requirements and randomization strategies.

## 3.5. Visits and evaluations

| ***Tests*** | ***Screening*** | ***Inclusion*** | **Day** | | | **Month** | |
| --- | --- | --- | --- | --- | --- | --- | --- |
| *Visits* |  | ***V1 = D1*** | ***V2*** | ***V3*** | **V4**8 | **V5** | **V6** |
| *Days* |  | *K-10 to K-7* | *K0 - K1* | *K4 to K7* | K12 to K16 | K24 to K32 | K60 |
| *Trial information* | X |  |  |  |  |  |  |
| *Inclusion - non-inclusion criteria* | X |  |  |  |  |  |  |
| *Informed consent form* |  | X |  |  |  |  |  |
| *Randomization* |  | X |  |  |  |  |  |
| *Demographic data, history of the tumor, medical and surgical history1*. |  | X |  |  |  |  |  |
| *Neodjuvant treatment* |  | X |  |  |  |  |  |
| *Injection of prolonged release pasireotide or placebo* |  | X |  |  |  |  |  |
| *Clinical evaluation, signs and symptoms 2* | X | X | X | X | X | X | X |
| *Adverse events 3* |  | X | *X* | *X* | *X* | *X* | *X* |
| *Surgical data 4* |  |  | X |  |  |  |  |
| *Postoperative data 5* |  |  |  | X |  |  |  |
| *Clinical evaluation 6* |  |  |  | X | X | X | X |
| *Permanent anatomopathological characteristics and adjuvant treatments 7* |  |  |  |  |  | X |  |
| *Routine lymphocele aspiration* |  |  |  |  |  | X |  |
| *Laboratory blood tests (pharmacokinetics)* |  | X |  |  | X |  |  |
| *ECG* |  | X |  |  | X |  |  |

1: demographic data (age, BMI), tumor history, medical and surgical history (breast surgery), concomitant medical diseases (diabetes, obesity), neo-adjuvant chemotherapy, tumor characteristics (TNM classification, histology, location)

2: weight, blood pressure, heart rate, fever.

*3: examination for skin reactions at the injection site (redness, pain, necrosis) and other adverse events.*

*4: type of procedure, duration, complications during surgery, compression dressing, type, number and location of drains.*

*5: daily and total drainage volume, date on which drains are removed and total drainage volume, postoperative complications (hematoma, skin necrosis, abscess, fever), presence of a lymphocele, lymphocele aspiration and duration of hospital stay.*

*6: number of lymphocyte aspirations, volume aspirated on each occasion, adjuvant chemotherapy start date. Skin test: redness, delayed healing, abscess, leakage.*

*7: histological type, grade, hormone receptors, Ki67, Her2, size of tumor, number of nodes removed, number of positive nodes, multifocal tumour, selected adjuvant treatments (chemotherapy and type of chemotherapy, number of cycles, hormone therapy, Herceptin® and radiotherapy)*

*8: If the V4 visit corresponds to more than 24 days after injection, this visit will be advanced in order to perform ECG and pharmacokinetic between 19 and 23 days after injection of pasiréotide LAR.*

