### 3.1.2. Study design

- The Ji data correspond to the length of time compared to the injection of pasireotide or placebo [J1 = day of injection], Ki data correspond to the duration of the procedure [K0=day on which surgery is performed].
- Screening: reporting and presurgical visit
  - Check for compliance with inclusion and non-inclusion criteria
  - Explanation of the trial to the patients
  - Issue of the Patient Information Letter
- Baseline visit (V1 = J1) 7 to10 days before surgery (K-10 to K-7):
  - Consent form signed
  - Injection of pasireotide or placebo by a consultation nurse who will not be present during subsequent visits since aspiration may be required.
  - Recording of adverse events
  - Blood sample for pharmacokinetic monitoring
  - ECG
- Visit V2 (day of surgery or day after surgery [K0 or K1]): collection of data concerning the operation (type of surgery, duration, intraoperative complications, type and number of drains)
  - Recording of adverse events:
- Visit V3 (day of discharge: K4 to K7 post-surgery): Summary of the daily collection of postoperative data:
  - The daily and total drainage volumes
  - Date on which drains were removed and overall duration of drainage
  - Postoperative complications (hematoma, skin necrosis, etc.)
  - Whether aspiration of a symptomatic lymphocele was required
  - Length of hospital stay
  - Recording of adverse events:
- Immediate postoperative visit (V4): 14+/- 2 days following surgery (K12 to K16)
  - The number of repeated lymphocele aspirations and the volume (patients requiring an aspiration will be seen during the interval between two consultations at the hospital and data will be colligated in the medical file. To ensure the lymphoceles sufficiency, a free phone number will be given to the patient in order that she could report any event if necessary.)
  - Recording of adverse events
  - ECG
  - Blood sample for pharmacokinetic monitoring
- Postoperative visit (V5): 28+/- 4 days following surgery (K24 to K32)
  - Routine lymphocele aspiration is considered positive if the volume aspirated exceeds 120cc.
  - The number of repeated lymphocele aspirations and the volume (patients requiring an aspiration will be seen during the interval between two consultations at the hospital and data will be colligated in the medical file.
  - Adjuvant chemotherapy start date, if required
  - Recording of adverse events
- Follow-up visits at two months (V6)
  - Recording of adverse events

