### 3.5.1. Schedule

- Screening: reporting and presurgical visit
- Baseline visit (V1) 7 to 10 days before surgery
- Visit V2 (K0 or K1 postoperative)
- Visit V3 (day of discharge: K4 - K7 postoperative)
- Immediate postoperative visit (V4): 14+/- 2 days following surgery
- Postoperative visit (V5): 28+/- 4 days following surgery
- Follow-up visits at two months (V6)

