### 3.5.2. Visit schedule

- Screening: reporting and presurgical visit
  - Check for compliance with inclusion and non-inclusion criteria
  - Explanation of the trial to the patients
  - Issue of the Patient Information Letter
- Baseline visit (V1) 7 to 10 days before surgery:
  - Consent form signed
  - Injection of pasireotide or placebo
  - Recording of adverse events
  - ECG
  - Blood sample for pharmacokinetic monitoring
- Visit V2 (K0 or K1 postoperative): collection of data concerning the operation (type of surgery, duration, intraoperative complications, type and number of drains)
  - Recording of adverse events:
- Visit V3 (day of discharge: K4 - K7 postoperative) Summary of the daily collection of postoperative data:
  - The daily and total drainage volumes
  - Date on which drains were removed and overall duration of drainage
  - Postoperative complications (hematoma, skin necrosis, etc.)
  - Whether aspiration of a symptomatic lymphocele was required
  - Length of hospital stay
  - Recording of adverse events:

It has been decided that drains will be removed when the daily drainage volume is less than 50 cc and that the maximum total duration of drainage will be 7 days. The drain will be emptied as from the 5th postoperative day.

- Immediate postoperative visit (V4): 14+/- 2 days following surgery. If the V4 visit corresponds to more than 24 days after injection, this visit will be advanced in order to perform ECG and pharmacokinetic between 19 and 23 days after injection of pasiréotide LAR.
  - The number of repeated lymphocele aspirations and the volume (patients requiring an aspiration will be seen during the interval between two consultations at the hospital and data will be colligated in the medical file. To ensure the lymphoceles sufficiency, a free phone number will be given to the patient in order that she could report any event if necessary.)
  - Recording of adverse events
  - Blood sample for pharmacokinetic monitoring
  - ECG
- Postoperative visit (V5): 28+/- 4 days following surgery
  - Routine lymphocele aspiration is considered positive if the volume aspirated exceeds 120cc.
  - The number of repeated lymphocele aspirations and the volume.
  - Adjuvant chemotherapy starting date, if required
  - Recording of adverse events:
- Follow-up visits at two months (V6)
  - Recording of adverse events:

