**3.5.4 Evaluation of medicinal dosages and of pharmacokinetic**

A pharmacokinetic study will be realized with a sample before injection at V1 (injection day) and a sample at V4 (J19-23 post-injection). If the V4 visit corresponds to more than 24 days after injection, this visit will be advanced in order to respect samples times. An electrocardiogram (ECG) will be done at the same time that sampling for pharmacokinetic.

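### The rule that moves V4 earlier starts one day too late: a visit on day 24 after injection misses the day 19 to 23 ECG and drug-sample window but is not moved

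*Protocol*

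**What the plan says.** Three parts of the protocol combine here.

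- **Visit timing.** Section 3.5.1 sets "Baseline visit (V1) 7 to 10 days before surgery", and V1 is the day of injection. Section 3.1.2 sets "Immediate postoperative visit (V4): 14+/- 2 days following surgery (K12 to K16", where K0 is the day of surgery.
- **Sampling window.** Note 8 to the table in section 3.5 asks for "ECG and pharmacokinetic between 19 and 23 days after injection", and section 3.5.2 gives the same window. Section 3.5.4 plans "a sample before injection at V1 (injection day) and a sample at V4 (J19-23 post-injection" and ties the ECG to the sampling time.
- **Trigger for moving the visit.** Note 8 applies "If the V4 visit corresponds to more than 24 days after injection". Section 3.5.2 uses the same condition. So does section 3.5.4, which also states the purpose: "more than 24 days after injection, this visit will be advanced in order to respect samples times".

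No section says what happens to a V4 that falls on exactly day 24.

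**The concern.** A rule meant to keep an assessment at or before day 23 has to act from day 24. This one acts from day 25. The trigger and the end of the window appear in the same sentence in note 8 and in section 3.5.2, so they disagree within a single instruction.

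The assessment has no back-up. The table in section 3.5 places ECG and pharmacokinetics only at V1 and V4, and the V1 sample is taken before injection with the ECG at the same time. V4 therefore carries the only scheduled post-injection ECG and the only post-injection drug level. QT prolongation is a visible safety concern in this protocol: section 3.3.2 excludes patients for QTcF above 450 msec, for risk factors for torsades de pointes and for QT-prolonging medication. A site that follows the trigger to the letter can record both measurements one day after the window has closed.

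**Working it through.** **Inputs**

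- Injection interval *d*: 7, 8, 9 or 10 days before surgery (sections 3.1.2 and 3.5.1).
- V4 day *k*: K12 to K16 (section 3.1.2 and the table in section 3.5).
- Window: days 19 to 23 after injection, both ends included (note 8, section 3.5.2).
- Trigger: strictly more than 24 days after injection (note 8, sections 3.5.2 and 3.5.4).

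**Formula.** Days from injection to V4 = *d* + *k*. There are 4 × 5 = 20 permitted whole-day combinations.

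| Interval *d* | Days after injection (K12 to K16) | In window (19–23) | Day 24: late, not moved | Days 25–26: moved |
|---|---|---|---|---|
| 7 | 19–23 | 5 | 0 | 0 |
| 8 | 20–24 | 4 | 1 (8 + 16) | 0 |
| 9 | 21–25 | 3 | 1 (9 + 15) | 1 |
| 10 | 22–26 | 2 | 1 (10 + 14) | 2 |
| **Total** | 19–26 | **14** | **3** | **3** |

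Check: 14 + 3 + 3 = 20. Six combinations fall after day 23, and the rule as written moves three of them. One of the three that it misses, 10 + 14, has V4 on its nominal day.

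**Does the day count matter?** Section 3.1.2 numbers the injection day J1, so a J number equals elapsed days + 1, and section 3.5.4 writes the window with a J. The possible readings are:

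| Window counted in | Trigger counted in | Out of window and not moved |
|---|---|---|
| elapsed days | elapsed days | day 24: 3 combinations |
| J numbers | J numbers | J24 (elapsed day 23): 4 combinations |
| J numbers | elapsed days | elapsed days 23 and 24: 4 + 3 = 7 combinations |
| elapsed days | J numbers | none |

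The gap closes only in the last reading. That reading needs two different counts for two limits that note 8 and section 3.5.2 express in the same words within one sentence.

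**With the trigger at more than 23 days**

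- Elapsed days for both limits: all 6 late combinations are moved and 0 remain out of window. Days that satisfy both K12 to K16 and days 19 to 23 are K12–K16, K12–K15, K12–K14 and K12–K13 for intervals of 7, 8, 9 and 10 days, that is 5, 4, 3 and 2 days.
- J numbers for both limits: J19 to J23 is elapsed days 18 to 22, and again 0 remain out of window. The days available are K12–K15, K12–K14, K12–K13 and K12, that is 4, 3, 2 and 1.
- Window in J numbers and trigger in elapsed days: 4 combinations (elapsed day 23) would still be missed. The new digit therefore works fully only if both limits use the same count.

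**The case against.** The strongest reply is that section 3.5.4 fixes the sampling time independently of the trigger. A site that drew the sample on day 24 would breach that section whether or not the instruction to advance the visit applied. The intent is clear, and a careful site would move a day-24 visit. This limits the harm. It does not reconcile the text, because the site then has one instruction giving the window and another, meant to enforce it, that leaves the visit in place.

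Second, the count of 3 in 20 depends on how days are numbered. That is right: it is 4 or 7 under other readings. It bears on the size and on how the correction should be worded. It does not make the gap disappear, except under the mixed reading that the sentence does not support.

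Third, one day may not matter. Section 1.1 describes an effective plateau after 10 days for the prolonged-release form, pharmacokinetics is not among the secondary objectives in section 2.2, and no decision rule depends on the exact ECG day. This stands, and it is why the point is minor.

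Fourth, the repeated 24 might be a deliberate one-day tolerance. The protocol states no such tolerance, and section 3.5.4 gives the aim as respecting the sampling times.

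**Conclusion.** The trigger is wrong as written, in all three places, by one day. Counting both limits in elapsed days and including both ends of the window, 3 of the 20 permitted calendar combinations are late and not moved. Counting both as J numbers, it is 4 of 20. Neither figure is an expected share of patients, because the protocol gives no distribution of injection intervals or visit days.

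The effect is a one-day overshoot of the only scheduled post-injection ECG and drug level. No measurement is lost, and neither the primary endpoint nor the sample size is touched. It is a minor correction, worth making because it is almost free.

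**What to change.** In note 8 to the table in section 3.5, in section 3.5.2 and in section 3.5.4, change the trigger from more than 24 to more than 23 days after injection.

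In section 3.5.4, replace the J19-23 notation with 19 to 23 days after injection, so that it matches the other two places, and state that days are elapsed days with the injection day as day 0. The sponsor should confirm that elapsed days were intended: under the J1 convention of section 3.1.2, J19 is 18 elapsed days, so this edit settles a one-day ambiguity and is more than cosmetic.

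The cost is one digit in three places and one aligned phrase. No procedure or visit is added, and every moved V4 can stay within K12 to K16.
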